### Pregnancy

Subjects must utiliz reliable contraception during the treatment and during follow-up period. A female subject must be instructed to stop taking the study medication and immediately inform the investigator if she becomes pregnant during the study. The investigator should report all pregnancies within 24 hours to the principal investigator/designee, using the Pregnancy Report CRF. The investigator should counsel the subject, and discuss the risks of continuing with the pregnancy and the possible effects on the fetus. Monitoring of the subject should continue until conclusion of the pregnancy. Pregnancies occurring up to 90 days after the completion of the study medication must also be reported to the investigator. Subjects that become pregnant during the treatment period will be withdrawn from the treatment period.

Pregnancy occurring in the partner of a male subject participating in the study should be reported to the investigator and principal investigator/designee. The partner should be counseled, the risks of continuing the pregnancy discussed, as well as the possible effects on the fetus. Monitoring of the subject should continue until conclusion of the pregnancy. A Pregnancy Report worksheet and Pregnancy Fax Coversheet should be completed and faxed to principal investigator/designee within 1 working day after learning of the pregnancy.

### Warnings and precautions

IFN may cause or aggravate fatal or life-threatening neuropsychiatric, autoimmune, ischemic, and infectious disorders. Subjects should be monitored closely with periodic clinical and laboratory evaluations. Therapy should be withdrawn from subjects with persistently severe or worsening signs or symptoms of these conditions. In many, but not all cases, these disorders resolve after stopping IFN therapy.

There are no adequate, controlled studies of any IFN in pregnant females. Therefore, extreme care must be taken to avoid pregnancy during the study in female subjects, and female partners of male subjects taking IFN. Females who are pregnant or breast-feeding will be excluded. A pregnancy test will be performed for each female of childbearing potential prior to baseline and be performed according to the schedules in Table 1.

# The complete statistical analysis plan

## Primary and secondary study endpoints

### Primary endpoints

The primary efficacy parameter is HBsAg loss as measured by the Roche Elecsys HBsAg II Quant assay (Roche Diagnostics, Penzberg, Germany; dynamic range 0.05-52,000 IU/ml), with both taken at end of treatment and 24 weeks after the end of treatment.

### Secondary endpoints

The secondary efficacy parameters include (at end of treatment and 24 weeks after the end of treatment)

1. HBsAg seroconversion
2. Proportion of patients who achieve HBV DNA < 1000 copies/ml
3. Quantitative HBsAg measurement
4. HBeAg seroconversion
5. ALT normalization

Histology improvement (option)

### Safety

Safety of the treatment will be evaluated by AEs (including SAEs), laboratory tests, vital signs (blood pressure, heart rate, temperature).

## Statistical methods

### Primary Variables

The primary efficacy parameter is HBsAg loss at end of treatment and 24 weeks after the end of treatment. Subjects with missing values for this parameter will be considered non-responders.

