| Co-Investigator: | [name], [name], [name], [name], [name], [name] |

SYNOPSIS OF PROTOCOL

| TITLE | Combination therapy of pegylated interferon-alpha-2b, nucleoside/nucleotide analogues (NAs) and GMCSF in NA-experienced chronic hepatitis B patients: A prospective, randomized open-label trial (Anchor study) |
| --- | --- |
| SPONSOR | The Chinese National Thirteenth Five Years Project in Science and Technology (2017ZX10202201) |
| INDICATION | NA-experienced CHB |
| OBJECTIVES | Primary: To compare the efficacy (HBsAg loss) and safety of pegylated interferon alfa-2b therapy plus entecavir (ETV) with or without GMCSF or ETV alone in NA-experienced CHB patients who had sustained HBV DNA suppression by ETV treatment. |
| TIRAL DESIGN | A multi-center, randomized, prospective, open-label Phase IV clinical trial. Patients will be randomized 1:1:1 in the IFN+ETV +GMCSF combination therapy group, IFN+ETV group or ETV group. |
| NUMBER OF PATIENTS | Total N 257 |
| TARGET POPULATION | The subjects who pre-treated by ETV for at least 1 year and achieved HBV DNA ≤10^3^ copies/ml & HBsAg <3000 IU/ml. Patients were excluded if they had previously developed drug resistance to ETV, or received IFN or systemic antiviral therapy within the previous 6 months. Patients were also excluded if they were coinfected with the human immunodeficiency virus, hepatitis C virus or hepatitis D virus or if they had decompensated liver disease (defined as a Child-Pugh Score B or C), pregnancy or lactation, or any other contraindication for IFN therapy |
| LENGTH OF STUDY | 96 weeks treatment  24 weeks follow up |
| DURATION OF STUDY | 42 months after first patient randomized |
| INVESTIGATIONAL PRODUCTS  DOSE/ROUTE/REGIMEN | Group 1: Entecavir 0.5mg once per day; P.O.  Group 2: Entecavir 0.5mg once per day (cessation at week 48); P.O. Pegylated interferon alfa-2b 180ug once per week; S.C.  Group 3: Entecavir 0.5mg once per day (cessation at week 48); P.O. Pegylated interferon alfa-2b 180ug per week; S.C. plus GM-CSF (Teerli, Xiamen Amoytop Biotech Co., Ltd, China) 75 μg once-daily for the first 5 consecutive days each month; S.C. |
| ASSESSMENT OF EFFICACY | Primary Endpoint:  HBsAg loss at Week 96.  Secondary Endpoint:   1. HBsAg seroconversion 2. Proportion of patients who achieve undetectable HBV DNA 3. Quantitative HBsAg measurement 4. HBeAg seroconversion 5. ALT normalization 6. Sustained virologic response at the end of follow-up |

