Focusing on increasing the rate of HBsAg loss, the central goal of national "Twelfth Five-Year" viral hepatitis plan, our study proposes a multi-target combination intervention to improve HBsAg loss rate for CHB patients who had received long-term NAs treatment but not achieved HBeAg seroconversion. Based on the data from previous OSST study, the sequential combination therapy of NAs and IFN are designed, and the immunomodulatory factor GM-CSF is added timely. It is planned to establish a cohort in multiple centers and fulfill the new treatment strategy.

This study intends to adopt a prospective, multi-center, randomized, controlled, open-labeled trial design. The enrolled CHB patients will be assigned to three treatment groups according to the principle of random (1:1:1). Patients in Group I are treated with ETV for 96 weeks; patients in Group II are treated with Peg-IFN for 96 weeks, combined with ETV during the first 48-week; Group III are treated with Peg-IFN for 96 weeks, combined with ETV and GM-CSF during the first 48-week. All patients will be followed-up for 24 weeks after treatment. It is expected that the HBsAg loss rate in Group II and III will increase by more than 10% compared with Group I after treatment, which indicates a better clinical outcome. The success of this project will improve the treatment efficacy of existing antiviral therapy, and enable CHB patients to safely stopping NAs in advance to avoid drug resistance. More importantly, amounts of CHB patients with suboptimal treatment efficacy will obtain HBeAg seroconversion even HBsAg seroconversion, which can reduce the occurrence of liver cirrhosis and liver cancer. It will produce huge social and economic benefits.

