## Clinical assessments and procedures

A baseline visit will be performed, and for subjects in three groups all baseline assessments and procedures must occur prior to administration of the first dose of study drug. Subjects will subsequently be seen for evaluation at the following timepoints:

During treatment period: Day 1, Week 2, 4, 8, 12, 16, 20, 24, 28, 32, 36, 40, 44, 48, 52, 56, 60, 64, 68, 72, 76, 80, 84, 88, 92 and 96

During follow-up: Week 24 post-treatment

Any subject who discontinues study treatment should return to complete assessments as per the Week 96 visit.

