### Analysis populations: ITT and mITT population

The ITT population shall include all subjects who receive at least one dose of study medication. For the ITT population, subjects will be analyzed according to the groups to which they were randomized.

A modified ITT (mITT) analysis was conducted, excluding patients who failed to meet inclusion criteria at baseline prior to randomization. Any patients including in mITT analysis who withdrew from the study, for whatever reason, was classified as a non-responder.

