### Efficacy Analysis

The primary and secondary efficacy analysis will compare efficacy among three groups.

The descriptive statistics depending on the type of variables will be as follows:

Quantitative variable: size, mean, standard deviation, minimum and maximum.

Qualitative, ordinal variables: frequency and percentage per class.

Response rates for primary and secondary endpoints were assessed by calculating percentages and 95% confidence intervals (CIs) for the ITT and mITT populations. Categorical variables were analyzed by the v2 test or Fisher’s exact test, and continuous variables were analyzed by t test or Wilcoxon test as appropriate. Logarithmic transformation was performed in the case of skewed data. Statistical analyses were conducted by SAS version 9.2.

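### The primary endpoint has one time point in the synopsis and two in the body, with no decision rule and no fixed week for patients who stop treatment early

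*Protocol*

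**What the plan says.** All places are in the protocol.

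- Synopsis, Assessment of Efficacy: one primary endpoint, "HBsAg loss at Week 96".
- Section 5.1.1 and section 10.1.1: HBsAg loss on the quantitative assay, "with both taken at end of treatment and 24 weeks after the end of treatment".
- Section 10.2.1, Primary Variables: "The primary efficacy parameter is HBsAg loss at end of treatment and 24 weeks after the end of treatment". Its missing-data rule follows: "Subjects with missing values for this parameter will be considered non-responders". The rule speaks of a single parameter although two times have just been named.
- Background and Rationale: "All patients will be followed-up for 24 weeks after treatment". With 96 weeks of treatment, the second time is Week 120 for a patient who completes.
- Table 1 schedules HBsAg at both Week 96 and Week 120, so both results will exist.
- Section 7.4: "Any subject who discontinues study treatment should return to complete assessments as per the Week 96 visit". Section 7.8 gives the same visit as the preferred course for patients who refuse further treatment. Section 7.4 describes follow-up relative to the end of treatment, whereas Table 1 and the synopsis use calendar weeks.
- Section 10.2.4: a patient in the modified ITT analysis "who withdrew from the study, for whatever reason, was classified as a non-responder".
- Section 10.2.5: categorical outcomes are analysed by a chi-square test "or Fisher’s exact test, and continuous variables were analyzed by t test or Wilcoxon test as appropriate". No significance level is given.

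**The concern.** Two gaps sit in the same definition.

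The first is the number of time points. The synopsis and the body disagree, and the body names two times without a rule. They could be co-primary (both needed), alternatives (either suffices), a per-patient composite (loss at both visits) or a ranked pair. Each gives a different response rate, error rate and power.

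The second is the date. If end of treatment means the day a patient actually stops, the primary assessment moves with that day. If it means scheduled Week 96, a patient who stopped early and was seen only at the discontinuation visit has no primary result.

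The trial is open-label and all these results will be visible, so whoever writes the report could choose among readings that the text equally allows. Responders are expected to be few: the protocol assumes 0–3% HBsAg loss on ETV. A handful of reclassified patients could therefore change the conclusion.

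**Working it through.** **No figure of the plan to reproduce.** The protocol attaches no error rate, power or single effect size to this endpoint. The 80–100 per group is described as a pilot size, so it can be neither confirmed nor refuted here.

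**Scoring of an early stopper.** Take a patient who stops treatment at Week 20 with HBsAg loss (an invented case).

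| Reading | Primary result | Score |
|---|---|---|
| End of treatment is the actual stop, using the section 7.4 visit | Week 20, then Week 20 + 24 = Week 44 | Responder at the first time |
| Scheduled Week 96, no result there (10.2.1) | Missing | Non-responder |
| Also withdrew from the study, modified ITT set (10.2.4) | Set by rule | Non-responder |

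The three routes give two distinct scores. One reclassified patient moves an arm's rate by 1/86 = 1.2 percentage points. The assumed ETV rate of 0–3% is itself only 0 to 2.6 patients (0.03 × 86).

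**Inputs for the decision-rule illustration.**
- n = 86 per arm: synopsis total 257 / 3 = 85.7.
- Null rate 8.5% in both arms: the HBsAg loss that the Background reports for the investigators' previous switch study.
- Two-sided 5% level: assumed.
- Persistence k of a Week 96 loss to Week 120, 70–90%: assumed.
- Two models, because the protocol gives no late-loss rate: no new losses after Week 96, or new losses that exactly replace those that revert, at rate (1 − k)p/(1 − p).

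**Upper bound for either time.** If the two tests were independent, 1 − 0.95² = 0.0975. They are not independent. In the replacement model the within-patient correlation is k − (1 − k)p/(1 − p). At p = 0.085 and k = 0.8 this is 0.8 − 0.2 × 0.0929 = 0.78. For two normal tests correlated at 0.8, the either-time error is 0.078.

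**Simulation, 400,000 runs per row, one pair of arms, no true difference.**

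| k | New losses | Chi-square, one time | Chi-square, either | Fisher, either |
|---|---|---|---|---|
| 0.7 | replace | 4.8% | 8.3% | 4.8% |
| 0.7 | none | 4.8% | 7.1% | 3.8% |
| 0.8 | replace | 4.9% | 7.7% | 4.5% |
| 0.8 | none | 4.8% | 6.7% | 3.8% |
| 0.9 | replace | 4.9% | 7.0% | 4.1% |
| 0.9 | none | 4.9% | 6.2% | 3.5% |

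Repeat runs move the last digit by about 0.1 point.

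**Power if both times must succeed, 10% versus 20%.** This contrast is only illustrative: 10–20% is the range that the protocol gives for the single IFN arm.
- One time, by formula: power = Φ[(Δ − 1.96·SE₀)/SE₁].
- SE₀ = √(2 × 0.15 × 0.85/86) = 0.0545.
- SE₁ = √((0.10 × 0.90 + 0.20 × 0.80)/86) = 0.0539.
- (0.10 − 1.96 × 0.0545)/0.0539 = −0.13, so power is 45%. Simulation agrees at 45%.
- Both times, k = 0.8, chi-square: 34% with replacement and 32% with no new losses.

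**The case against.** The strongest case on the other side has five parts.

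- **The error argument depends on the test.** Section 10.2.5 also permits Fisher's exact test, and at these low rates the either-time error then stays below 5%. Requiring both times is conservative and inflates nothing. This stands. The defect is an undefined endpoint more than a large excess of false positives.
- **A reader might infer a much larger error over all three pairs of arms.** The documents do not support charging that to the two time points. Three unadjusted pairs at a single time already give about 12%, which is a separate question. The calculation also needs ETV to share the 8.5% rate, against the protocol's own 0–3%.
- **A reader might infer that the plan replaces Week 96 with the discontinuation visit.** It does not say so. Section 7.4 asks for a visit with Week 96 content, Table 1 fixes visits by calendar week, and stopping treatment is not the same as withdrawing from the study. What stands is that nothing says the visit is additional, so the floating reading remains open.
- **A reader might infer that scoring will differ by arm.** More early stopping on Peg-IFN is plausible from the stopping rules in section 8.1, but the protocol gives no discontinuation rates, so no size can be put on it.
- **The protocol calls the trial a pilot, and a separate analysis plan may exist.** The first softens the error-rate argument. The second does not cure the fault, because the protocol's own sections contradict each other and section 10 is titled as the complete analysis plan.

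**Conclusion.** The concern holds and the text is wrong as written. One place fixes a single primary time point, three places fix two, and no rule joins them. For early stoppers with HBsAg loss, the text allows both possible scores.

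For one pair of arms, counting either time gives an error of about 6.2–8.3% with chi-square and 3.5–4.8% with Fisher's exact test. Requiring both lowers chi-square power from about 45% to 32–34% in the 10% versus 20% example at 80% persistence. These figures rest on an assumed 5% level, assumed persistence and 86 per arm. The contradiction itself rests on none of them. It should be settled before any comparative result is seen.

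**What to change.** Reconcile the synopsis with sections 5.1.1, 10.1.1 and 10.2.1:

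1. Name HBsAg loss at the scheduled Week 96 visit as the sole primary endpoint.
2. Make HBsAg loss at Week 120 the first secondary endpoint, tested only if Week 96 is significant.
3. In sections 7.4 and 7.8, state that the discontinuation visit is additional to the scheduled visits and does not replace Week 96.
4. State that patients who stop treatment but remain in the study are scored on their Week 96 and Week 120 results.
5. In sections 10.2.1 and 10.2.4, impute non-response only when the scheduled result is missing.

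Co-primary endpoints with both required, a per-patient composite or a split of the significance level would also remove the contradiction, if stated everywhere. Week 96 alone is the simplest, since the synopsis already has it, and it avoids the power loss of requiring both.

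The cost is wording in these sections and up to two further blood draws per early stopper, at visits already in Table 1. No treatment rule changes.

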### Secondary Variables

All secondary variables will be determined at end of treatment and 24 weeks after the end of treatment.

1. HBsAg positivity (defined as presence of anti-HBs) and seroconversion (defined as loss of HBsAg and presence of anti-HBs)
2. Proportion of patients who achieve undetectable HBV DNA
3. Quantitative HBsAg measurement
4. HBeAg seroconversion (defined as absence of HBeAg and presence of HBeAb in

HBeAg negative patients)

1. ALT normalization (defined as ALT measure ≤ ULN)
2. Sustained virologic response at the end of follow-up

Histology improvement (option)

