### Secondary Endpoint

The secondary efficacy parameters include (at end of treatment and 24 weeks after the end of treatment)

1. HBsAg positivity and seroconversion
2. Proportion of patients who achieve undetectable HBV DNA
3. Quantitative HBsAg and it’s decline
4. HBeAg seroconversion
5. ALT normalization

6. Sustained virologic response at the end of follow-up

Histology improvement (option)

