# Schedule of assessments and procedure

## Schedule of assessments

Table 1 Schedule of assessments

| Flowchart | Screening | Treatment period | | | | | | | | | | | | | | | | | | | | | | | | | | Follow-up | |
| --- | --- | --- | --- | --- | --- | --- | --- | --- | --- | --- | --- | --- | --- | --- | --- | --- | --- | --- | --- | --- | --- | --- | --- | --- | --- | --- | --- | --- | --- |
| Visit | V1 | V2 | V3 | V4 | V5 | V6 | V7 | V8 | V9 | V1  0 | V1  1 | V1  2 | V1  3 | V1  4 | V1  5 | V1  6 | V1  7 | V1  8 | V1  9 | V2  0 | V2  1 | V2  2 | V2  3 | V2  4 | V2  5 | V2  6 | V2  7 | V28 | V29 |
| Study  Weeks  (w) | -8w-0d | 0d | 2w  ±  3d | 4w  ±  3d | 8w  ±  3d | 12 w  ±  3d | 16 w  ±  3d | 20 w  ±  3d | 24 w  ±  3d | 28 w  ±  3d | 32 w  ±  3d | 36 w  ±  3d | 40 w  ±  3d | 44 w  ±  3d | 48 w  ±  3d | 52 w  ±  3d | 56 w  ±  3d | 60 w  ±  3d | 64 w  ±  3d | 68 w  ±  3d | 72 w  ±  3d | 76 w  ±  3d | 80 w  ±  3d | 84 w  ±  3d | 88 w  ±  3d | 92 w  ±  3d | 96 w  ±  3d | 108 w  ±  7d | 120 w  ±  7d |
| Written informed  consent | X |  |  |  |  |  |  |  |  |  |  |  |  |  |  |  |  |  |  |  |  |  |  |  |  |  |  |  |  |
| Collect medical  history | X |  |  |  |  |  |  |  |  |  |  |  |  |  |  |  |  |  |  |  |  |  |  |  |  |  |  |  |  |
| Physical  examination | X | X | X | X | X | X | X | X | X | X | X | X | X | X | X | X | X | X | X | X | X | X | X | X | X | X | X | X | X |
| Signs and symptoms | X | X | X | X | X | X | X | X | X | X | X | X | X | X | X | X | X | X | X | X | X | X | X | X | X | X | X | X | X |
| Blood  coagulation | X |  |  |  |  |  |  |  | X |  |  |  |  |  | X |  |  |  |  |  | X |  |  |  |  |  | X |  | X |
| HCG^1^ |  | X |  |  |  |  |  |  |  |  |  |  |  |  | X |  |  |  |  |  |  |  |  |  |  |  | X |  |  |
| Routine urine  test^2^ | X | X |  |  |  |  |  |  | X |  |  |  |  |  | X |  |  |  |  |  | X |  |  |  |  |  | X |  |  |
| Abdominal  ultrasound | X |  |  |  |  |  |  |  | X |  |  |  |  |  | X |  |  |  |  |  | X |  |  |  |  |  | X |  |  |
| ECG | X |  |  |  |  |  |  |  |  |  |  |  |  |  | X |  |  |  |  |  |  |  |  |  |  |  | X |  |  |
| Chest X ray | X |  |  |  |  |  |  |  |  |  |  |  |  |  | X |  |  |  |  |  |  |  |  |  |  |  | X |  |  |
| Ophthalmo-  logical  examination | X |  |  |  |  | X |  |  | X |  |  |  |  |  | X |  |  |  |  |  | X |  |  |  |  |  | X |  |  |
| AFP | X |  |  |  |  |  |  |  |  |  |  |  |  |  | X |  |  |  |  |  |  |  |  |  |  |  | X |  | X |

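### Table 1 schedules no HBV DNA test at Week 120, although the protocol sets its HBV DNA secondary endpoint at 24 weeks after the end of treatment

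*Protocol*

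**What the plan says.** Three places in the protocol fix when the HBV DNA endpoint is read.

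- The Secondary Endpoint section opens with "The secondary efficacy parameters include (at end of treatment and 24 weeks after the end of treatment" and lists undetectable HBV DNA.
- The Secondary endpoints section of the statistical chapter uses the same two time points and gives the item as "Proportion of patients who achieve HBV DNA < 1000 copies/ml".
- The Secondary Variables section states "All secondary variables will be determined at end of treatment and 24 weeks after the end of treatment" and lists "Proportion of patients who achieve undetectable HBV DNA".

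The first and third of these, and the synopsis, also list "Sustained virologic response at the end of follow-up".

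On the length of follow-up, Background and Rationale says "All patients will be followed-up for 24 weeks after treatment". Table 1 has two follow-up columns, headed "108 w ± 7d | 120 w ± 7d" (visits V28 and V29). The synopsis also lists visits at both weeks. The Clinical assessments and procedures section lists only one: "During follow-up: Week 24 post-treatment".

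**The concern.** An endpoint needs an assay at its own time point. Sites work from the schedule table, so a test that is blank there will generally not be done. If Week 120 HBV DNA is not ordered, a named secondary endpoint has no data at its stated time in any arm, and no later analysis plan can supply them.

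The matter has some substance for this trial. The Background gives relapse after stopping therapy as a main weakness of existing regimens, and expects a successful result to let patients stop nucleos(t)ide analogues safely. Whether virologic suppression lasts to the end of follow-up bears on that expectation. Substituting the Week 108 value would answer a question about 12 weeks after treatment, not 24.

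**Working it through.** No power or sample-size figure is involved. The check compares the time points the endpoints require with those the schedule provides.

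**Step 1: the required weeks.** Treatment ends at Week 96 in all three arms (Overview of study design). Follow-up is 24 weeks. The second time point is 96 + 24 = Week 120, which is V29.

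**Step 2: the scheduled weeks.** Table 1 has 29 visit columns, V1 to V29. Each row below was split into cells and matched to those columns. Each has exactly 29 cells, so none has visibly lost or gained a cell when the PDF was read.

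| Table 1 row | Week 96 (V27) | Week 108 (V28) | Week 120 (V29) |
|---|---|---|---|
| HBV DNA | X | X | blank |
| HBsAg | X | blank | X |
| HBeAg | X | blank | X |
| HBsAb | X | blank | X |
| Biochemistry (includes ALT) | X | X | X |
| Serum sample | X | X | X |
| Immunologic parameters | X | X | blank |

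The full HBV DNA row is screening, day 0, and Weeks 12, 24, 36, 48, 60, 72, 84, 96 and 108.

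**Step 3: comparison.** Of the five markers behind the main secondary endpoints (HBsAg, HBsAb, HBeAg, HBV DNA, ALT), four are scheduled at Week 120. HBV DNA is not. One of its two required time points is covered.

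**Step 4: what the schedule gives instead.** The last HBV DNA falls 108 − 96 = 12 weeks after treatment, which is 12/24 = half of the stated interval.

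**Step 5: does anything else order the test?** Table 3 includes HBV DNA among the post-screening laboratory tests, but the Laboratory assessments section leaves the timing to Table 1. That section sends only HBsAg to the central laboratory, so no central run would supply the value. The notes under Table 1 add no visit. The Serum sample row shows a draw at Week 120, but the protocol does not assign that sample to HBV DNA.

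**Step 6: the visit lists.** The synopsis and Table 1 both include Week 108. The follow-up list under Clinical assessments and procedures omits it, and Week 108 is the only post-treatment visit with an HBV DNA test.

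**The case against.** The best answer is that this is a one-cell slip. HBsAg, HBeAg and HBsAb are all blank at Week 108 and marked at Week 120, so the HBV DNA mark may simply sit one column too far to the left. That is plausible, but it cannot be shown: the row has its full 29 cells, and the Immunologic parameters row has the same pattern. In either case the table that sites follow disagrees with the endpoint text.

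The objection is stronger against some wider readings, which the documents do not support:

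- **No virologic data after treatment.** A reader might infer this from the visit list under Clinical assessments and procedures. But the synopsis and Table 1 both include Week 108, and laboratory tests follow Table 1. What is missing is the 24-week value. HBV DNA is also scheduled at Weeks 60, 72, 84, 96 and 108, after entecavir has ended at Week 48 in the two interferon arms, although Weeks 60 to 96 are still on peginterferon.
- **A sustained response of 0% in every arm through non-responder imputation.** The missing-value rule under Primary Variables covers the primary parameter only. The rule under Analysis populations covers patients in the modified ITT analysis who withdraw. Neither reaches a secondary assay that was never scheduled.
- **The endpoint cannot be measured.** Serum is drawn at Week 120. The test is unscheduled, not impossible.
- **Sustained virologic response certainly fails too.** The term is not defined, and the Secondary endpoints list in the statistical chapter omits it. Its dependence on HBV DNA is inferred from its name.

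**Conclusion.** The point stands as an internal contradiction: the protocol is wrong as written. The HBV DNA secondary endpoint at 24 weeks after treatment has no scheduled measurement for any of the planned patients (257 in the synopsis), and the only HBV DNA test after treatment comes at 12 weeks. This rests on a direct cell count of Table 1 and on the endpoint sections, with no numerical assumption.

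Sustained virologic response is affected only on the assumption that it is judged by HBV DNA at the end of follow-up. The primary endpoint is untouched. Because the gap is one time point of a secondary endpoint and is easily closed, it should be fixed, but it does not threaten the trial's main comparison.

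**What to change.** 1. Mark HBV DNA at V29 (Week 120) in Table 1 and keep the Week 108 mark.
2. Add Week 108 to the follow-up visits under Clinical assessments and procedures, so that the list agrees with the synopsis and Table 1.
3. If patients have already passed Week 120, assay the serum drawn at that visit. This assumes that it was stored suitably for HBV DNA and in sufficient volume, which the protocol does not say. If it was not, report the endpoint openly as 12 weeks after treatment.

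The cost is about one HBV DNA assay per patient: 257 × 1 = 257 assays at the synopsis figure, or 240 to 300 over the planned range. Neither the visit nor the blood draw is new.

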## Assignment to treatment groups

All the eligible patients were randomly assigned in a 1:1:1 to one of three groups. We used interactive web response system (IWRS) for computer-generated randomisation sequences with a predefined stratification scheme. Randomisation was stratified by HBeAg (positive or negative) state and gender (male or female) at enrolment. A patient will be enrolled in the study and assigned a patient number after all protocol eligibility requirements have been met. The investigator will use the appropriate patient’s Case Report Form (CRF) and record the patient’s allocated treatment or treatment number in the CRF. It is the investigator’s responsibility to ensure that each patient receives the assigned treatment.

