## Inclusion Criteria

1. Male and female patients aged 18 to 65 years old at baseline;
2. Subjects who experienced ETV treatment for at least 1 year;
3. Serum HBV DNA≤1000 copies/ml;
4. HBsAg positive;
5.
[figure not shown]

[figure not shown]
ALT >2 ULN but <10 ULN and HBeAg positive before NAs treatment;
6. Negative urine or serum pregnancy test (for women of childbearing potential) documented within the 24-hour period prior to the first dose of test drug;
7. Absence of cirrhosis determined by liver ultrasound;
8. Agree to participate in the study and sign the patient informed consent.

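### Three secondary endpoint definitions (HBeAg seroconversion, HBV DNA response, anti-HBs) are wrong or inconsistent as written; the primary endpoint is not affected

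*Protocol*

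**What the plan says.** All places are in the Protocol.

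- **HBeAg seroconversion.** Secondary Variables reads "HBeAg seroconversion (defined as absence of HBeAg and presence of HBeAb in" and continues on the next line "HBeAg negative patients". The synopsis, Secondary Endpoint (under End points) and Secondary endpoints (in the statistical section) list HBeAg seroconversion with no restriction. Assignment to treatment groups states: "Randomisation was stratified by HBeAg (positive or negative) state and gender (male or female) at enrolment".
- **HBV DNA.** Secondary endpoints, in the statistical section, reads "Proportion of patients who achieve HBV DNA < 1000 copies/ml". Secondary Endpoint, under End points, reads "Proportion of patients who achieve undetectable HBV DNA"; the synopsis and Secondary Variables agree with the latter. Inclusion criterion 3 is "Serum HBV DNA≤1000 copies/ml".
- **Anti-HBs.** Secondary Variables reads "HBsAg positivity (defined as presence of anti-HBs". The same label appears without a definition in Secondary Endpoint and in the Efficacy paragraph of Clinical assessments and procedures.

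**The concern.** A secondary endpoint should be open to change during the trial in the patients who are counted, and its name should match what is measured. Each of these three items fails one of those tests. The HBeAg rate would be calculated in the wrong patients. The HBV DNA item has two incompatible definitions, one of which repeats an entry condition. The anti-HBs item carries the name of the marker whose disappearance is the primary endpoint, so a favourable result would read as an unfavourable one.

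This goes beyond detail left to a later document, because the definitions are stated, and stated wrongly. The trial is open-label. If the text is left alone, someone must choose between readings when results by arm may already be visible.

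**Working it through.** No figure in the protocol has to be reproduced, and no sample size or error rate depends on these endpoints. The check sets the definitions beside the entry conditions.

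**1. HBeAg seroconversion**

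- Who enters: both HBeAg-positive and HBeAg-negative patients, since HBeAg state at enrolment is a stratification factor.
- Inclusion criterion 5 requires HBeAg positivity before nucleos(t)ide analogue treatment. An HBeAg-negative entrant therefore lost HBeAg before the trial.
- The Background describes the target as patients on long-term treatment who have not seroconverted, and hopes that they will.
- Reading A, HBeAg-negative at enrolment: patients HBeAg-positive at enrolment contribute nothing to the denominator. Of those counted, 100% meet the absence-of-HBeAg half at entry. The HBeAb half is met at entry by an unknown share, because no criterion concerns anti-HBe.
- Reading B, HBeAg-negative at the time of assessment: the absence-of-HBeAg half is redundant. The denominator becomes a post-randomisation outcome and mixes patients who lost HBeAg on study with those who lost it beforehand.
- Neither reading gives the seroconversion rate among patients who can lose HBeAg on study.

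**2. HBV DNA**

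| Place | Role | Condition |
| --- | --- | --- |
| Synopsis (target population); Inclusion Criteria | entry | at most 1000 copies/ml |
| Objectives of study; Overview of study design; Overview under Target population | entry | below 1000 copies/ml |
| Secondary endpoints (statistical section) | endpoint | below 1000 copies/ml |
| Synopsis; Secondary Endpoint; Secondary Variables | endpoint | undetectable, no limit given |

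- With the strict entry wording, 100% of eligible patients in every arm meet the below-1000 endpoint at entry.
- With the at-most wording, the only eligible patients who do not are those at exactly 1000.
- The below-1000 proportion starts at essentially 100% and can only stay there or fall. It measures maintained suppression, so *achieve* is the wrong verb.
- The undetectable version is a different endpoint with no threshold. Laboratory assessments assigns HBsAg to the central laboratory and other parameters to local laboratories, so the threshold could differ between the 6 centres.

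**3. Anti-HBs**

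- The label names the antigen; the parenthesis defines the antibody.
- All entrants must be HBsAg positive, and the primary endpoint is HBsAg loss. By its label a higher rate means failure; by its definition a higher rate is favourable.
- The definition is explicit, so an analyst who follows it measures the intended marker. Only the name is wrong.

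**The case against.** The best defence is that the intent can be recovered. *Negative* in the HBeAg definition is probably a slip for *positive*: three other listings carry no restriction, and the Background names the intended patients. The anti-HBs definition already identifies the right marker. All these endpoints are secondary in a study that calls itself a pilot, and no decision rule rests on them. This stands as an argument about severity. It does not make the text correct.

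Four stronger readings are tempting, and the documents do not support them.

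- *HBeAg-negative entrants are all seroconverters before dosing.* They meet only the HBeAg half. A patient without HBeAb at entry could still gain it, and the protocol gives no anti-HBe prevalence from which to estimate a rate.
- *HBV DNA below 1000 copies/ml is uninformative.* Two arms stop entecavir at week 48, and the endpoint is read at end of treatment and 24 weeks later. Whether suppression lasts can depend on treatment.
- *All these rates only describe the baseline population.* Nothing says that entrants carry anti-HBs, so that item is not shown to be met at entry, and the HBV DNA point above also counts against the general claim.
- *ALT normalization has the same fault.* The definition, "ALT normalization (defined as ALT measure ≤ ULN", is neither contradictory nor reversed. Restricting it to patients with raised baseline ALT is denominator detail that a statistical analysis plan may settle, and the protocol does not say how many entrants have normal ALT.

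One objection also limits the remedy. After at least one year of entecavir, some patients may already be undetectable at entry, so changing to undetectable does not by itself make the endpoint one of new response. The documents do not give that share.

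**Conclusion.** The point holds for three definitions, at should-fix level. The HBeAg item is the most serious: on its natural reading it counts none of the patients who are HBeAg-positive at enrolment, and everyone it does count meets half of the definition at entry. The HBV DNA item is an internal contradiction, and one of its two versions is met at entry by essentially all eligible patients. The anti-HBs item is a mislabel and no more.

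This assumes that *HBeAg negative* refers to status at enrolment (the alternative reading is no better) and that randomised patients meet the entry criteria. The protocol does not give the split by HBeAg state, so the number of patients left out cannot be calculated. HBsAg loss and its analysis are unaffected.

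**What to change.** 1. **HBeAg seroconversion:** define it as HBeAg loss plus presence of HBeAb among patients HBeAg-positive at enrolment, using the existing stratification value. The cost is a smaller denominator and a wider confidence interval.
2. **HBV DNA:** use undetectable HBV DNA in all sections, with one stated assay limit that every local laboratory can report, and show the proportion undetectable at baseline beside it. If below 1000 copies/ml is kept, report it separately as maintained suppression.
3. **Anti-HBs:** rename the item anti-HBs positivity in Secondary Variables, in Secondary Endpoint and in the Efficacy paragraph of Clinical assessments and procedures.

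These are wording changes, best made before secondary endpoints are tabulated by arm. One data check is needed. Table 1, as it could be read, marks HBV DNA at week 108 but not at week 120, whereas the endpoint is due 24 weeks after treatment (96 + 24 = 120). Compare this with the original table. If a separate statistical analysis plan already has the right definitions, the protocol should be aligned with it.
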